### Study objectives

The objectives of this trial are: (1) to compare the clinical and psychosocial effectiveness of in-group modality and individual modality of pain neuroscience education (PNE) in patients with CLBP; (2) To analyze the influence of social determinants of health on post-treatment results.

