#### Sample size

Sample size calculation was performed with G*Power 3.1. A repeated measures analysis of variance (ANOVA) model with within-between interaction, was used. Assuming an alpha risk of 0.05, a power of 0.95, a correlation between repeated measures of 0.5, a 10% drop-out rate, and a small effect size (0.26), a total of 20 participants per group (three groups) were required. The effect size estimate was based on a previous study about education compared to physical therapy for the FABQ outcome (Marshall et al., 2022) and the recommended effect size for clinical studies (Lakens, 2013).

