### Data analysis

#### Statistical approach

The analysis of the data will be blinded, as each subject and condition will be coded by a consultant who will not be involved in the investigation. SPSS software version 25.0 will be used for all analyzes (SPSS Inc. Armonk, NY, USA). Data will be reported as mean with SD or median with interquartile range. Statistical analyzes were performed on an intention-to-treat basis, with imputation of missing data using the average of the remaining participants.

Normality tests will be performed using the Shapiro–Wilk test given the number of subjects needed for each group. In addition, the homogeneity of variance and the sphericity of the data will be determined. In the case of not assuming any of these assumptions, the Green-Hausser correction will be used for the interpretation of subsequent analyzes. A three-way repeated measures ANOVA will be conducted to analyze both primary and secondary outcomes. The factors considered in this analysis will include time and intervention. Additionally, the third factor will encompass variables such as employment status, education level, or income. In case of significant interaction, a two-way repeated measures ANOVA (time (pre-post) × intervention (in-group PNE, individually PNE, no intervention)) will be performed for each employment status (employed or unemployed). Furthermore, a two-way repeated measures ANOVA (time (pre-post) × intervention (in-group PNE, individually PNE, no intervention)) will be performed for each educational level (high or low). Lastly, a two-way repeated measures ANOVA (time (pre-post) × intervention (in-group PNE, individually PNE, no intervention)) will be performed for income (≤USD 545, or >USD 545). If interactions are detected in any of the 2-way ANOVAs, a *post-hoc* analysis will be conducted using multiple pairwise comparisons employing a *t*-test corrected by Bonferroni. The significance level will be set at 5%.

A stepwise multiple linear regression will be performed to estimate the influence of changes in primary and secondary outcomes. In each model, adjustments will be made for employment status, educational level, and income. In this analysis, the aforementioned variables will be sequentially incorporated into each model.

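### The interaction that opens the within-stratum ANOVAs is not named, so the plan allows a uniform PNE effect to look like an influence of a social determinant

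*Protocol article*

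**What the plan says.** The Statistical approach section of the protocol article fits, for primary and secondary outcomes, a three-way repeated measures ANOVA with time, intervention and a third factor: employment status, education level or income. The next step is "In case of significant interaction, a two-way repeated measures ANOVA" of time (pre-post) by intervention for each employment status. Two further sentences plan the same two-way analysis by education level and by income, and neither repeats a condition. Pairwise testing comes last: "If interactions are detected in any of the 2-way ANOVAs, a *post-hoc* analysis" follows, using Bonferroni-corrected t-tests.

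Objective 2 is "To analyze the influence of social determinants of health on post-treatment results", and the Introduction hypothesises that the determinants influence the effects in both experimental groups. No sentence says which result will count as such an influence, and no step compares one stratum with the other. The stepwise regression is described as adjusting for the determinants; no intervention × determinant term is named.

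The Sample size section concerns a different term: "A repeated measures analysis of variance (ANOVA) model with within-between interaction, was used", with "a power of 0.95".

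**The concern.** A three-way model of this kind contains four interactions: time × intervention, time × determinant, intervention × determinant, and the three-way term. Only the three-way term asks whether a determinant changes the treatment effect over time. Time × intervention is the treatment effect itself. If it may open the stratum analyses, they will be run in most trials where PNE works, whether or not the determinant matters.

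The stratum ANOVAs cannot answer objective 2 on their own. The null hypothesis in each is that there is no time × intervention effect in that stratum. Two strata with the same true effect can easily fall on opposite sides of 5%. Because pairwise tests follow only where a two-way ANOVA shows an interaction, the report could then show detailed contrasts for one level and none for the other. A reader could take that as evidence that the determinant modifies the effect.

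**Working it through.** **Inputs from the article.** Alpha 0.05, power 0.95, correlation 0.5, 10% dropout, f = 0.26 (taken as Cohen's f), three groups (Sample size). Three measurement times (Data collection and management), but pre-post in the two-way ANOVAs (Statistical approach). The total N is inconsistent, so all three values are used: 3 × 20 = 60 (Sample size), 69 (Abstract), and 3 × 33 = 99 (Abstract, per-arm figures). **Assumed, because not given:** the larger stratum holds 50%, 70% or 80% of participants, split equally across arms.

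**1. The plan's own figure.** For a within-between interaction, λ = f²·N·m/(1−ρ), df1 = (k−1)(m−1), df2 = (N−k)(m−1).
- m = 3: N = 51 gives λ = 0.0676 × 51 × 3/0.5 = 20.7 and power 0.961. 51/0.9 = 56.7, so 57, or 19 per group against the stated 20.
- m = 2: N = 60 gives λ = 0.0676 × 60 × 2/0.5 = 16.2 and power 0.949, with no dropout allowance.

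The stated size is closely reproduced, and it is a size for time × intervention.

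**2. Power inside a stratum, same effect in both (N = 60, pre-post, so λ = 0.2704·n).**
- 30/30: λ = 8.11 in each; power 0.672 and 0.672.
- 42/18: λ = 11.36 and 4.87; power 0.835 and 0.414.

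**3. Chance that exactly one stratum is significant, with no condition applied:** p₁(1−p₂) + (1−p₁)p₂.
- 30/30: 2 × 0.672 × 0.328 = 0.441.
- 42/18: 0.835 × 0.586 + 0.165 × 0.414 = 0.558.

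Equal strata already give 44%, so low power within each stratum is a cause as well as unequal size.

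**4. The two readings of the condition.** Simulation with 20,000 trials per setting, change scores, a uniform f = 0.26, and type III tests. Under the broad reading, time × intervention, time × determinant or the three-way term at p < 0.05 opens the strata.

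| N | Larger stratum | Power, larger / smaller | Broad: strata opened | Broad: opened and exactly one significant | Three-way only: opened and exactly one significant |
|---|---|---|---|---|---|
| 60 | 50% | 0.67 / 0.67 | 95.2% | 43.6% | 3.1% |
| 60 | 70% | 0.84 / 0.42 | 91.8% | 51.6% | 2.7% |
| 60 | 80% | 0.89 / 0.25 | 82.4% | 56.7% | 2.6% |
| 69 | 50% | 0.77 / 0.72 | 97.4% | 37.3% | 2.7% |
| 69 | 70% | 0.89 / 0.49 | 95.2% | 49.0% | 2.6% |
| 69 | 80% | 0.92 / 0.34 | 89.8% | 56.6% | 2.6% |
| 99 | 50% | 0.88 / 0.91 | 99.7% | 18.5% | 1.8% |
| 99 | 70% | 0.97 / 0.67 | 99.2% | 33.3% | 1.7% |
| 99 | 80% | 0.99 / 0.49 | 97.3% | 48.4% | 1.9% |

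A repeat simulation gave 43–56%, 36–55% and 18–48% for the broad reading, and 1.4–3.1% for the three-way reading. The ranges quoted elsewhere cover both runs.

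**5. Sensitivity (N = 69, 70% share, broad reading).** Arm effects in steps instead of two equal active arms: 48%. Half the effect (f = 0.13): 27%. No effect: 5%. If the stratum ANOVAs used all three times, power would be higher. With no condition applied, discordance would then be 36–68% (N = 60), 27–63% (N = 69) and 9–46% (N = 99), against 44–69%, 38–66% and 19–54% for pre-post.

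**The case against.** The best defence is convention. A three-way ANOVA followed by two-way ANOVAs at each level of the third factor, and then by pairwise tests, is the usual step-down from a significant three-way interaction. The education and income sentences can be read as continuing the same conditional list. On that reading the misleading pattern arises in only about 1–3% of trials per determinant. The planned three-way model also already contains the correct test. All of this stands, and it limits the point to an unnamed term and an unstated rule of inference.

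It does not settle the matter, because the narrow reading creates its own difficulty. The section describes no two-way ANOVA in the whole sample; the only described route to pairwise comparisons runs through the strata. With a uniform effect, the three-way term would be non-significant in about 95% of trials per determinant. The in-group versus individual comparison, which is objective 1, would then not be reached by that route. This gives a reader reason to include time × intervention among the interactions that open the strata.

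A condensed article may leave detail to the full protocol. Here, however, the sequence is set out explicitly, and the fault lies in the stated rule.

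Three stronger inferences are not supported:
- That any interaction does open the strata: the article leaves the term open.
- That the trial will judge influence by comparing stratum p-values, or will report that PNE fails in disadvantaged groups: no sentence says so. No stratum shares are given, so it is not known which level would be the smaller.
- That unequal stratum sizes alone produce the pattern: the equal-strata rows in the table show otherwise.

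**Conclusion.** The point holds as an ambiguous condition combined with a missing rule of inference. Depending on which interaction is meant, the chance of a one-stratum-only result under an identical effect moves from about 1–3% to somewhere between 18% and 57% per determinant, and there are three determinants and several outcomes. The figures rest on assumed stratum shares, an equal split across arms, the pre-post contrast, and a true effect as large as the planned f = 0.26; a smaller effect lowers them. The direction of a spurious difference cannot be predicted. The trial could report a false influence of a determinant; the article does not commit it to doing so. Because objective 2 and a stated hypothesis depend on this step, the wording should be settled before the data are analysed.

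**What to change.** Amend the Statistical approach section in three places.

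1. State that the stratum ANOVAs for a given determinant are run only if the time × intervention × determinant term for that determinant is significant, and apply this to employment, education and income alike.
2. State that influence of a determinant is concluded only from that term, reported as the difference in treatment effect between its levels with a 95% CI. Present stratum results as descriptive estimates.
3. State that the overall time × intervention test and its Bonferroni pairwise comparisons, which serve objective 1, are done in the whole sample and do not depend on any determinant.

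This costs a few sentences and no new data. The downside is fewer stratum-specific p-values. The trial is not sized for the three-way term, and the interval for the difference will show how much can be learned. The ordinary error rate remains: about 5% per determinant, or 1 − 0.95³ = 14.3% over three determinants for one outcome if the tests are independent.

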In chronic pain rehabilitation, it is essential to address the factors mentioned above (McCracken, 2005). In this sense, the biomedical approach to education may promote the fear-avoidance model (Louw et al., 2011), while the pain neuroscience education (PNE) promotes patients’ understanding of chronic pain and changes maladaptive thoughts and cognitions (Moseley, 2002; Meeus et al., 2010) with a biopsychosocial approach limiting the fear-avoidance model (Louw et al., 2016b). PNE has shown positive results on the kinesiophobia, catastrophizing, pain intensity, disability, and physical performance in patients with CLBP (Moseley, Nicholas & Hodges, 2004; Ryan et al., 2010; Louw et al., 2011; Malfliet et al., 2017; Rufa, Beissner & Dolphin, 2018; Núñez Cortés et al., 2023a; Nuñez Cortés et al., 2023b). A recent meta-analysis has shown that the in-group PNE had better results than individual PNE for kinesiophobia (Romm et al., 2021), and it has been identified, in other types of health education, that there are greater benefits in those people who received the in-group intervention (Riemsma, Taal & Rasker, 2003), probably supported by the fact that educational sessions conducted in-group modality can facilitate learning through social observation of positive behaviors exhibited by other members within the group (Romm et al., 2021; Salazar-Méndez et al., 2024). However, there are no primary studies comparing the two PNE modalities directly. On the other hand, despite increasing evidence that SDH are influential factors in clinical health outcomes to a greater extent than the quality and availability of medical care (Daniel, Bornstein & Kane, 2018), there are no studies that analyze specifically the influence of SDH factors (*e.g.*, educational level) on the effectiveness of PNE (Salazar-Méndez et al., 2024).

We hypothesize that there will be significant differences in favor of the intervention in-group modality compared to the individual modality. Furthermore, the effects will be influenced by the social determinants of health in both experimental groups.

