The calculation of Cohen’s d will be performed to determine the effect size (ES) of all intragroup variables. Consider a small effect size if it is less than or equal to 0.2; medium of 0.3 to 0.5 and large of 0.5 to 0.8 (Jacob, 1992).

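### No whole-sample contrast or between-arm estimate is planned for in-group versus individual PNE: pairwise tests run only inside social-determinant strata, and effect sizes are within-group

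*Protocol article*

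**What the plan says.** The Protocol article's first objective (Study objectives) is "to compare the clinical and psychosocial effectiveness of in-group modality and individual modality of pain neuroscience education (PNE) in patients with CLBP". The Introduction gives it a direction: the authors expect that "there will be significant differences in favor of the intervention in-group modality compared to the individual modality". Neither statement is limited to a social subgroup.

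Statistical approach then sets out an order of tests:

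1. A three-way repeated measures ANOVA for every outcome, with time, intervention and one social determinant of health (SDH: employment, education or income) as factors.
2. "In case of significant interaction, a two-way repeated measures ANOVA" of time by intervention, run for each employment status. The same ANOVA is then listed for each educational level and for income.
3. "If interactions are detected in any of the 2-way ANOVAs", Bonferroni-corrected pairwise t-tests.

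The section also plans a regression: "A stepwise multiple linear regression will be performed to estimate the influence of changes in primary and secondary outcomes", adjusted for the three SDH variables. It ends with Cohen's d, to be calculated "to determine the effect size (ES) of all intragroup variables".

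**The concern.** The pairwise tests are the only step that separates in-group from individual PNE, and they hang on ANOVAs run inside SDH levels. If PNE works equally well at every SDH level, nothing in the stated order leads to a comparison of the two formats in all randomised patients. If the comparison is reached, it is reached in a subgroup, possibly one picked out by its own p-value.

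The effect sizes do not fill the gap. A within-arm d mixes the effect of treatment with natural course and regression to the mean (entry requires average pain of 3 to 8 out of 10), and it is not a randomised comparison. The trial could therefore report on its main hypothesis without any estimate of the difference that the hypothesis is about.

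**Working it through.** **Which steps could give the Objective 1 contrast?**

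- Three-way ANOVA: it contains time × intervention on the whole sample, but as a three-arm omnibus test. It can be significant because PNE differs from usual care. It is fitted once per SDH factor, so there are three such p-values, and none has a planned follow-up.
- Two-way ANOVAs: each one listed is by SDH level.
- Pairwise t-tests: conditional on those two-way ANOVAs.
- Regression: no arm term is named.
- Cohen's d: within group.

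None gives in-group minus individual in the whole sample.

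**The plan's own sample size.** Inputs from Sample size: f = 0.26, alpha 0.05, power 0.95, correlation 0.5, three groups, 10% drop-out. Time points: three (Data collection and management). For the within-between interaction, λ = f²·N·m/(1−ρ), df1 = (k−1)(m−1), df2 = (N−k)(m−1).

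- With m = 3, the smallest N is 49, rounded to 51 (17 per group). Then λ = 0.0676 × 51 × 3/0.5 = 20.7 and power is 0.96. After drop-out, 17/0.9 = 18.9, so 19 per group against the stated 20. With f = 0.25 it is exactly 20.
- The calculation therefore reproduces approximately, and it sizes the whole-sample omnibus interaction (power 0.98 at N = 60). It does not size the in-group versus individual pair.

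**An assumed effect for the pair.** The documents give none; the 0.26 comes from education versus physical therapy. If f = 0.26 is spread over three equally spaced arms at two times (the ANOVAs are labelled pre-post), adjacent arms differ by d = f·√6 = 0.26 × 2.449 = 0.637 SD. At ρ = 0.5 the SD of change is √(2(1−0.5)) = 1 outcome SD.

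**Direct whole-sample test.** Two-sample t on change, alpha 0.05/3 = 0.0167 (family of three arm pairs assumed), non-centrality d·√(n/2). The Abstract gives both 69 in total (23 per arm) and 33 per arm, and Sample size gives 20.

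| Per arm | Power, whole sample | Power, stratum holding half of each arm (assumed) |
|---|---|---|
| 20 | 32% | 14% |
| 23 | 38% | 16% |
| 33 | 55% | 25% |

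**The plan's route.** With no SDH modification, a three-way term is significant by chance in 5% of trials per factor, or 1 − 0.95³ = 14.3% for at least one of three independent factors. Simulations on change scores (arm means 0, 0.637 and 1.274 SD; binary SDH factors with prevalence 30–50%; 23 or 33 per arm) gave:

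| Reading of the gate | Pairwise stage reached | Difference detected in some stratum |
|---|---|---|
| Only the three-way term opens it, for all three factors | about 14–17% | about 8–12% |
| Education and income ANOVAs ungated | about 97–99% | about 43–60% |
| Time × intervention or the three-way term opens it | 97–98% (23 per arm) | 48–50% (23 per arm); 62% (33 per arm, 30% prevalence) |

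The last two rows exceed the direct test's 38% and 55% only because up to six strata are searched. If 30% have low education, that stratum has about 0.3 × 23 = 7 patients per arm.

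**The case against.** **The gate may be wide open.** The article does not name the interaction that triggers the follow-up, and the education and income ANOVAs can be read as unconditional. A reader might infer that about 86% of trials (1 − 0.143) never reach the pairwise tests. That holds only on the narrowest reading and is not established. This part of the objection stands, so the loss must be given as a range. It does not rescue the plan, because every reading keeps the pairwise tests inside strata.

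**There is a whole-sample test.** A reader might also infer that the trial could end with no test of intervention at all. The documents do not support that: the omnibus time × intervention term uses all participants and would be significant in about 97% of trials at 23 per arm in the scenario above. What is missing is the pairwise contrast and its estimate.

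**Objective 2 is covered.** The three-way interaction does address whether SDH modify the effect. The regression sentence is unclear about its predictors, so the absence of a named arm term is not evidence that SDH modification goes unexamined.

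**An article condenses.** This would excuse silence. Here the article fixes an explicit order of tests, and that order does not lead to its first objective.

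**Side points.** The d labels ("medium of 0.3 to 0.5 and large of 0.5 to 0.8") share 0.5 and leave 0.2–0.3 and values above 0.8 without a label, which is cosmetic. Preferring baseline adjustment to change scores is a matter of efficiency. Neither carries the point.

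**Conclusion.** The point holds in this form: followed as written, the plan gives no whole-sample contrast, estimate or confidence interval for in-group versus individual PNE, and its only effect sizes are not randomised comparisons. This follows from the text alone and needs no assumed effect.

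The size of the loss is conditional. It rests on 0.64 SD of change between the PNE arms, no SDH modification, and three independent SDH factors at 30–50%, none of which is in the documents. On that basis the stated route detects the difference in about 8–12% of trials on the narrow reading and about 43–62% on the looser ones, the latter through multiple small strata. The defect should be corrected before analysis, since it concerns the main hypothesis.

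**What to change.** In Statistical approach, make the primary analysis one whole-sample model of FABQ over time by arm, adjusted for baseline FABQ. Test a prespecified in-group versus individual contrast at a named follow-up time, whatever any SDH interaction shows. Follow it with each PNE arm versus control, Bonferroni-corrected, and state whether the primary contrast belongs to that family.

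Report between-arm differences and between-arm d with 95% CI as the effect sizes, and keep the within-group d as description only.

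For Objective 2, keep the arm × time × SDH interaction, name it explicitly as the term tested, and label all stratified results exploratory.

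The cost is a change of analysis wording and the demotion of subgroup results to exploratory. No new data are needed. The change does not make the trial large enough for this contrast: with 80% power at two-sided 0.05, the smallest detectable difference on change scores is 0.84 SD at 23 per arm and 0.70 SD at 33 (0.99 and 0.81 SD with Bonferroni over three pairs). The confidence interval should therefore carry the interpretation.

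### No full-sample comparison of in-group with individual PNE is planned, although it is the trial's hypothesis and first objective; the only pairwise tests sit inside social strata

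*Protocol article*

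**What the plan says.** All references are to the protocol article.

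- **Hypothesis (Introduction):** "there will be significant differences in favor of the intervention in-group modality compared to the individual modality".
- **First objective (Study objectives):** "to compare the clinical and psychosocial effectiveness of in-group modality and individual modality" of PNE. The influence of social determinants is the second objective.
- **Sample size:** a repeated measures ANOVA "model with within-between interaction, was used", for three whole groups with no social strata.
- **Statistical approach, step 1:** a three-way repeated measures ANOVA with time, intervention and one social factor (employment, education or income).
- **Step 2:** "In case of significant interaction, a two-way repeated measures ANOVA" of time by intervention "will be performed for each employment status (employed or unemployed"). Two further sentences plan the same ANOVA by educational level and by income class. Neither carries a condition of its own.
- **Step 3:** Bonferroni-corrected pairwise t-tests "If interactions are detected in any of the 2-way ANOVAs".
- **Regression:** "In each model, adjustments will be made for employment status, educational level, and income". No treatment-arm term is named.
- **Effect size:** Cohen's d is planned for the "effect size (ES) of all intragroup variables", that is, within groups.

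**The concern.** The stated sequence serves the second objective (do social factors modify the effect?) and reaches the first only as a by-product. Every two-way ANOVA is stratified, and pairwise tests follow only those. The regression and Cohen's d do not fill the gap, since neither is described as comparing the arms.

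The three-way model does contain a time by intervention term on the full sample. It tests all three arms together, so it can be significant only because PNE differs from usual care. It does not isolate in-group against individual, and no contrast is planned after it.

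If in-group delivery is better to about the same degree in everyone, which is the plain form of the hypothesis, the plan would answer from part of the sample, at a Bonferroni-reduced level, and for one social class. The randomised data would allow a direct estimate in everyone.

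**Working it through.** **1. The plan's own figure.** Inputs from Sample size: f = 0.26, correlation 0.5, alpha 0.05, power 0.95, three groups. For the within-between interaction, λ = f²·N·m/(1−ρ), df1 = (k−1)(m−1), df2 = (N−k)(m−1).

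- Two measurements (the pre-post form named in Statistical approach), N = 60: λ = 0.0676 × 60 × 2 / 0.5 = 16.2, df 2 and 57, power 0.949.
- Three measurements: N = 51 gives power 0.961. Inflated for 10% dropout this is 57, or 19 per group.

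The stated 20 per group is therefore about right, but for the three-arm omnibus interaction on whole groups. It says nothing about the modality contrast or about strata.

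**2. Assumptions for the comparison.** The document gives no modality effect, so these are assumed: change-score SD 1; in-group better than individual by 0.5 SD in everyone; control midway, so means are 0.5, 0 and 0.25; three independent social factors split 50/50. Arm sizes are 20 (Sample size), 23 (the Abstract's 69 / 3) and 33 (the Abstract's arm size).

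**3. Direct full-sample test.** Two-sample t on change, two-sided 5%, noncentrality d·√(n/2):

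- n = 20: 0.5 × √10 = 1.58, power 0.338
- n = 23: 0.5 × √11.5 = 1.70, power 0.382
- n = 33: 0.5 × √16.5 = 2.03, power 0.516

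For d = 0.3 to 0.8 the power is 17–76% at 23 per arm and 23–89% at 33 per arm.

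**4. How often a three-way gate opens.** With a uniform benefit there is no true three-way interaction, so each gate opens at its 5% error rate. For at least one of three independent factors: 1 − 0.95³ = 0.143.

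**5. The planned route, by simulation.** With pre-post data, time by intervention is a one-way ANOVA on change scores, and the three-way test is the arm by factor interaction on change scores. Each stratum then needs a significant two-way interaction and a t-test at 0.05/3.

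| Reading of the condition | Some pairwise step reached (n = 20, 23, 33) | In-group advantage significant in some stratum |
|---|---|---|
| All stratum ANOVAs gated by the three-way interaction | 11%, 12%, 13% | 7%, 7%, 9% |
| Only employment gated | 41%, 44%, 53% | 24%, 28%, 38% |
| None gated | not tabulated | 28%, 32%, 44% |
| Direct full-sample test | always | 34%, 38%, 52% |

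**6. Sensitivity.**

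- With control lowest (means 1.0, 0.5, 0), the all-gated reading again gives 7%, 7%, 9%. The employment-only reading reaches a pairwise step in 82%, 87%, 95% of trials and finds an in-group advantage in 25%, 29%, 40%.
- If the gate may also be opened by the full-sample time by intervention term, the advantage is found in 22%, 25%, 36% (control midway) or 28%, 33%, 46% (control lowest), still within strata.
- With 70/30 splits the all-gated figures are 6%, 7%, 8%.
- When the modalities are equal and both beat control by 0.5 SD, a false modality claim in some stratum occurs in about 3% of trials if all are gated and in 7–8% if none is.

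**The case against.** The strongest reply has four parts.

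**The wording is open.** The condition on a significant interaction grammatically governs only the employment sentence, and the section does not say which interaction is meant. This stands. A reader might infer that the trial would usually report no modality comparison at all. The text does not support that as a general statement: it follows only if all three stratum analyses wait for a three-way interaction. On the employment-only reading with control lowest, a pairwise step is reached in 82–95% of trials.

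**The power loss may be small.** With no gating, 28–44% is not far below 34–52%. That is true, but the 28–44% is a win in at least one of six strata. It carries a 7–8% false-claim rate when the modalities are equal, and it still gives no full-sample estimate.

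**The authors may have meant pairwise tests after the full-sample interaction.** That would be an ordinary three-arm choice, with 18%, 21% and 33% chance of showing the advantage. The section does not say it.

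**A condensed article may leave the contrast to the full protocol.** This would be a fair answer to silence. Here, however, the article sets out the sequence down to the trigger and correction of the post-hoc tests, and that sequence goes around the main comparison. Reported group means and SDs would let a reader derive a difference, but that is not a planned analysis.

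**Conclusion.** The point holds on every reading of the text as written. The hypothesis and first objective have no named full-sample contrast, and the only planned pairwise tests are Bonferroni-corrected and confined to social strata. That much rests on the wording alone.

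The size of the loss depends on the reading. Against 34–52% for a direct test, the chance of showing a 0.5 SD in-group advantage in some stratum is 7–9% in the worst case, 24–38% with only employment gated and 28–44% with no gating. These figures rest on the assumed effect, factor splits, independence and control position, none of which the document gives. The 7–9% is a worst case and should not be quoted as what the plan implies.

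**What to change.** In Statistical approach:

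- Prespecify the in-group versus individual difference in FABQ change, in the full randomised sample, as the primary contrast. Report it with a 95% confidence interval and test it at 5%, not conditional on any interaction.
- Treat the PNE-versus-control contrasts as secondary.
- Report the social-factor interactions and stratum comparisons separately, as exploratory analyses for the second objective, and state which interaction (if any) triggers them.
- Add a between-group effect size for the primary contrast beside the within-group Cohen's d.

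Which FABQ subscale and visit to name, and how to divide alpha among the secondary contrasts, are separate choices for the sponsor.

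**Cost:** analysis text only, with no new patients, visits or data. The control contrasts become secondary. The direct test still has only 34–52% power for 0.5 SD, so the confidence interval should carry the conclusion.
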